# Effectiveness of Kinesio Taping Combined With Neuromuscular Control Exercises on Pain and Function in Knee Osteoarthritis: A Multicenter Assessor‐Blinded Randomized Controlled Trial Protocol

**DOI:** 10.1002/hsr2.73125

**Published:** 2026-09-07

**Keywords:** kinesio taping, knee osteoarthritis, neuromuscular control exercise

## Abstract

**Background and Aims:**

Knee osteoarthritis (KOA) is a leading cause of functional impairment and decreased quality of life. Exercise is the recommended approach; however, adjunct interventions such as kinesio taping (KT) have gained attention for potential to reduce pain, improve proprioception, and enhance functional performance. Despite its growing clinical use, research on the effectiveness of combining KT with neuromuscular control exercises (NCE) in KOA remains limited. Therefore, this study aimed to assess the effectiveness of KT combined with NCE in reducing pain and improving functional outcomes in KOA.

**Methods:**

This randomized controlled trial is recruiting 80 participants with KOA. Participants are randomly allocated (1:1) to either an experimental group receiving KT combined with NCE or a control group receiving sham KT with NCE. Both groups are undergoing supervised intervention sessions three times per week for 8 weeks. Primary outcomes include pain intensity (Visual Analog Scale, VAS), pressure pain threshold (PPT—digital pressure algometer), and functional status (Western Ontario and McMaster Universities Osteoarthritis Index, WOMAC). Secondary outcomes include lower limb muscle strength (modified sphygmomanometer), knee range of motion (goniometer), and functional mobility (Timed Up and Go test, TUG). Outcomes are planned to be assessed at baseline, post‐intervention (8 weeks), and follow‐up (6 months). Repeated‐measures ANOVA will assess group, time, and group × time interaction effects, with between‐group differences and 95% CIs reported according to the intention‐to‐treat principle.

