
Therefore, the primary objective of this randomized controlled trial (RCT) is to evaluate the impact of 8 weeks of KT combined with NCE on pain reduction and functional improvement in patients suffering from KOA. Additionally, we intend to examine the impact of KT and NCE on other outcome measures, such as muscle strength, ROM, and functional mobility. We also aimed to assess the potential long‐term advantages of integrating KT with NCE beyond the immediate post‐intervention period, through a 6‐month follow‐up, and to assess the safety of this intervention. We hypothesize that participants receiving KT in addition to NCE will demonstrate significantly greater improvements in pain, physical function, and neuromuscular performance than those receiving sham KT with NCE.

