### Research Question

1.1

Among adults aged 45–70 years with radiographically confirmed KOA, does KT combined with an NCE program, compared with sham KT combined with the same exercise program, lead to greater improvements in pain, physical function, and relevant outcomes immediately after the 8‐week intervention and at 6‐month follow‐up?

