##### Functional Status

2.6.1.3

Functional status is being assessed using the Western Ontario and McMaster Universities Osteoarthritis Index (WOMAC), a validated instrument for assessing KOA. It includes 24 items across pain (ICC = 0.86), stiffness (ICC = 0.68), and physical function (ICC = 0.89), with sub‐scores of pain (0–20), stiffness (0–8), and physical function (0–68), totaling 96 [25].

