### Sample Size Calculation

2.7

G*Power, version 3.1.9.7 (University of Kiel, Kiel, Germany), was used to determine the required sample size for this study. The calculation indicates that a total of 68 participants are required, with an effect size (ES) of 0.61 for the functional outcomes, an *α* level of 0.05, and a power of 0.80 [29]. Therefore, each group requires 34 participants. After accounting for a 15% dropout rate, the number of participants in each group is increased to 40, resulting in a final estimated total of 80 participants.

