### Statistical Analysis

2.8

All statistical analyses will be performed using SPSS (Statistical Package for the Social Sciences), version 25 (IBM Corp., Armonk, NY, USA). Descriptive statistics will be presented as frequencies, percentages, means, and standard deviations, as appropriate. For between‐group comparisons of baseline characteristics, independent‐samples *t* tests will be used for continuous variables, and Pearson's Chi‐square (*χ*
^2^) tests will be used for categorical variables. Changes in outcome measures across the three assessment time points will be evaluated using repeated‐measures analysis of variance, with group, time, and group × time interaction effects examined to assess differences in trajectories between the intervention groups. Where appropriate, post hoc comparisons will be performed with adjustment for multiple comparisons. ESs will be estimated using partial eta squared (ηp^2^) for the repeated‐measures analyses and Cohen's d for pairwise comparisons, with Cohen's d values of 0.20, 0.50, and 0.80 interpreted as small, moderate, and large effects, respectively. Between‐group mean differences will be reported with corresponding 95% confidence intervals (CIs) to enhance the precision and clinical interpretability of the estimates. All analyses will follow the intention‐to‐treat principle, including all randomized participants in the analysis according to their assigned groups. Missing data will be addressed using multiple imputation under a missing‐at‐random assumption. A two‐sided *p*‐value of < 0.05 will be considered statistically significant.

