## Results

3

This study is a protocol for a RCT; therefore, no outcome data have been collected, and results are not yet available. It is anticipated that both KT combined with NCE and sham KT with NCE will improve primary outcomes, including pain intensity, PPT, and functional status. Secondary outcomes are expected to improve lower‐limb muscle strength, knee ROM, and functional mobility. Between‐group analyses will assess whether the addition of KT provides superior clinical and statistical benefits compared with sham KT with NCE at post‐intervention (8 weeks) and follow‐up (6 months). Data on treatment adherence, adverse events, and intervention feasibility will also be reported. Final results will be disseminated through peer‐reviewed journals and scientific conferences.

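### Three unranked primary outcomes are each judged at two-sided 0.05 with no rule across them, so the chance of at least one false positive is up to 14.3% if any one may carry the claim

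*Protocol article*

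**What the plan says.** The abstract reads "Primary outcomes include pain intensity (Visual Analog Scale, VAS), pressure pain threshold", followed by WOMAC. Section 2.6.1 lists the same three under the primary heading, and neither place ranks them. WOMAC is described "with sub‐scores of pain (0–20), stiffness (0–8), and physical function (0–68), totaling 96"; no one of these scores is named as the primary one.

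Section 2.8 plans a repeated-measures ANOVA for the outcome measures over three assessments, examining group, time and their interaction. It sets a single two-sided 0.05 threshold. On multiplicity it says: "Where appropriate, post hoc comparisons will be performed with adjustment for multiple comparisons". It names no method and does not say which comparisons are covered.

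On timing, the research question (Section 1.1) asks about benefit "immediately after the 8‐week intervention and at 6‐month follow‐up", and Section 3 likewise lists both times. The Introduction puts the 8-week effect in the primary objective and then adds: "We also aimed to assess the potential long‐term advantages of integrating KT with NCE beyond the immediate post‐intervention period".

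The sample size (Section 2.7) was calculated "with an effect size (ES) of 0.61 for the functional outcomes". The article contains no order of testing, no division of alpha, and no statement of whether one, some or all primary outcomes must succeed.

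**The concern.** A threshold of 0.05 gives a 5% error rate for one test. With three primary outcomes at that threshold and no rule linking them, the trial can report a positive primary result on whichever outcome crosses the line. The error rate of that overall claim is then above 5%, by an amount that the plan does not state.

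The trial was sized on function alone. An isolated result on VAS or PPT, with WOMAC not significant, would therefore be a finding on an outcome for which no power was stated, at an error rate that was not controlled. The Conclusion expects the findings to inform clinical guidelines, so it matters whether such a result counts as confirmation.

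**Working it through.** **The plan's own figure.** The article gives no familywise error rate. The figure it does give is the sample size: d = 0.61, alpha 0.05, power 0.80, 34 per group.
- Two-sample t-test, one-sided 0.05: 34 per group, 68 in total. This reproduces the stated number.
- Two-sided 0.05: 44 per group, 88 in total. This does not.
- Dropout: 34 / (1 − 0.15) = 40 per group. This reproduces.

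The one-sided match is a separate matter. It is used here only to set the power baseline for the fix: at two-sided 0.05, power is 0.70 with 34 per group and 0.77 with 40.

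**Inputs for the error rate.** Three primary outcomes (Abstract; Section 2.6.1), with WOMAC counted once; two-sided 0.05 (Section 2.8). The article gives no correlations between outcomes or between times, so these are assumptions, varied from 0 to 0.8.

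**One test per outcome, any success counts.**
- Independent outcomes, either direction: 1 − 0.95³ = 1 − 0.857 = 14.3%.
- Independent outcomes, false claims favouring KT only: 1 − 0.975³ = 1 − 0.927 = 7.3%, against 2.5% for one test.
- Correlated outcomes, by multivariate-normal simulation (300,000 draws), and the planned group × time F test, by simulation (40 per group, three times, time correlation 0.5, 20,000 trials):

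| Inter-outcome correlation | Three z-tests | Group × time F test, three outcomes |
|---|---|---|
| 0 | 14.3% (exact) | 14.0% |
| 0.3 | 13.6% | 13.7% |
| 0.5 | 12.5% | 13.1% |
| 0.7 | 11.0% | 11.3% |
| 0.8 | 9.8% | not run |

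The inflation is therefore present in the planned model itself and does not depend on how the time points are handled.

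**Adding the second time point (3 × 2 = 6 contrasts).**

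| Correlations (outcome, time) | No adjustment | Bonferroni over the two times within each outcome |
|---|---|---|
| 0, 0 | 1 − 0.95⁶ = 26.5% | 1 − 0.975⁶ = 14.1% |
| 0.5, 0.5 | 22.0% | 12.0% |
| 0.8, 0.8 | 14.9% | 8.1% |

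If the post hoc adjustment covers time points within an outcome, adding 6 months does not push the rate above the three-outcome figure. What remains is the uncontrolled multiplicity across outcomes.

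**The case against.** **The six-test figure.** A reader might infer six unadjusted tests and an error rate of 22% to 26%. The article does not support that. Contrasts at 8 weeks and 6 months after a repeated-measures ANOVA are naturally read as post hoc comparisons, and Section 2.8 promises adjustment for those. The fault there is the unstated scope, not a demonstrated absence of control.

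**Equal time points.** A reader might also call the two times co-equal. Sections 1.1 and 3 do not rank them, but the Introduction gives 6 months an additional role after the 8-week primary objective.

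**WOMAC sub-scores.** Counting these as further primary tests goes too far. Section 2.6.1.3 describes how the instrument is scored and does not say that each score will be tested as primary.

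**Either ANOVA effect.** If a significant group effect or a significant interaction on any outcome counted as success, simulation gives 21% to 27%. The article lists the effects to be examined but does not say that either one suffices.

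**Any-of or all-of.** Section 2.8 gives a significance threshold, not a success criterion, and the hypothesis in the Introduction joins its domains with a conjunction. If all three outcomes had to succeed, the error rate would not be inflated, although power was considered for function only. This objection stands to the extent that 14.3% is conditional on the any-of reading.

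**Left to an analysis plan.** Procedural detail may sit in a document not shown. But the article itself fixes three primaries and one threshold, and confines its multiplicity sentence to post hoc comparisons. That is a stated rule with the wrong error rate, not merely an omitted detail.

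**Conclusion.** The point holds for the three primary outcomes. With one test each at two-sided 0.05 and any success counting, the chance of at least one false positive is up to 14.3%, nearly three times the nominal rate (14.3 / 5 = 2.9). It is about 10% to 14% over assumed correlations of 0.8 to 0, so even strongly correlated outcomes leave it near double 5%. These figures count both directions. Restricted to false claims for KT, the maximum is 7.3% against 2.5%, the same ratio.

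The result rests on the any-of reading, on counting WOMAC once, and on correlations that the article does not supply. About 26% is an upper bound for independent, wholly unadjusted contrasts at both times and should not be quoted as the plan's error rate.

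**What to change.** Choose one of two rules before unblinding, and name the 8-week between-group contrast as the deciding test.

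1. **Fixed sequence.** Name the WOMAC score to which the 0.61 refers. Test it at 8 weeks at two-sided 0.05; then VAS at 8 weeks; then PPT at 8 weeks, each only if the one before is significant. The functional endpoint loses no power. The cost is that VAS and PPT can be claimed only after WOMAC succeeds, which places pain second although the objective names it first.
2. **Holm across three primaries.** Order the three 8-week p-values and compare the smallest with 0.05/3 = 0.0167, the next with 0.025 and the largest with 0.05, stopping at the first failure. Any outcome can then lead, but each loses some power. At the 0.0167 step, power for d = 0.61 is 0.53 with 34 per group and 0.61 with 40, against 0.70 and 0.77 at two-sided 0.05.

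Under either rule, make the 6-month contrasts secondary and state that the post hoc adjustment covers time points within an outcome, with the method named.

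Recruitment began in September 2025 (Section 2.2), and participants and therapists are not blinded (Section 2.4). Changing the status or order of primary outcomes is therefore a substantive change. Record it as a dated amendment to the protocol and the registry entry, stating that the statistician was still blinded and what data had been seen. No extra data collection is needed.

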**Results:**

The trial is expected to generate evidence on whether adding KT to NCE yields greater improvements in pain modulation, physical function, and mobility in KOA.

**Conclusions:**

This study will address a crucial evidence gap in multimodal, non‐pharmacological rehabilitation for KOA. Findings could support evidence‐based clinical decisions and provide a cost‐effective addition to exercise therapy, especially in resource‐limited settings like Bangladesh. Results might also guide future multicenter trials and standardized rehabilitation protocols for KOA.

**Trial Registration:**

CTRI/2025/08/093317 [Registered on: 20/08/2025]; trial registered prospectively.

AbbreviationsBMIBody Mass IndexCCICharlson Comorbidity IndexCONSORTConsolidated Standards of Reporting TrialsICCIntraclass Correlation CoefficientKOAKnee OsteoarthritisKTKinesio TapingNCENeuromuscular Control ExerciseRCTRandomized Controlled TrialROMRange of MotionSPIRITStandard Protocol Items: Recommendations for Interventional TrialsSPSSStatistical Package for the Social SciencesTUGTimed Up and Go TestVASVisual Analog ScaleWOMACWestern Ontario and McMaster Universities Osteoarthritis Index

## Introduction

1

Knee osteoarthritis (KOA) is one of the most prevalent forms of osteoarthritis, affecting approximately 365 million individuals worldwide [1]. It is characterized by synovitis, cartilage degeneration, and the formation of osteophytes, involving both contractile (muscle) and non‐contractile (cartilage, bone, ligament, tendon, synovium, meniscus) structures [2, 3]. KOA has become a significant cause of impairment among the elderly [4]. As the global elderly population continues to grow, an increasing number of individuals suffering from KOA are experiencing pain, oedema, stiffness, and functional impairments. Current studies estimate that around 18% of elderly men and 27% of elderly women suffer from KOA. Furthermore, these figures are anticipated to increase in the upcoming decades [5]. This condition impairs joint and muscle function, causing balance and gait issues [6]. Therefore, KOA is less avoidable than commonly believed.

Current KOA treatments aim to alleviate relevant symptoms through various methods, such as pharmacological, non‐pharmacological, and surgical interventions [4]. Non‐pharmacological options include manual therapy, physiotherapy modalities, taping techniques, and therapeutic exercises, all of which are utilized to treat KOA [7]. Among these, the utilization of kinesio taping (KT) has gained increasing prevalence among patients with KOA. [name] pioneered the development of the KT treatment in Japan during the 1970s [4]. KT has the potential to enhance muscular strength and improve knee condition. KT is an elastic adhesive tape applied to the skin. It is proposed that pain and function be influenced through altered cutaneous afferent input, proprioceptive modulation, neuromuscular facilitation, and potential effects on local circulation and lymphatic flow. Patients with KOA may benefit from KT, as it can alleviate pain, reduce swelling, improve ligament function, increase range of motion (ROM), and stabilize the knee joint [8, 9]. KT is gaining recognition as a physical treatment for KOA, with more clinicians and therapists adopting it [9]. However, evidence regarding KT's mechanism and effectiveness remains hypothetical, with mixed evidence reported in the literature. Although some high‐quality research has been conducted on KT in KOA patients, the overall conclusion about its impact remains inconclusive [5]. A 2013 systematic review states that KT interventions are not recommended for these musculoskeletal conditions [10]. Conversely, three meta‐analyses have demonstrated that KT can reduce pain and improve knee function compared to sham KT [11, 12, 13]. Another study in 2020 highlighted the significant impact of KT compared with physiotherapy on pain and functional improvement [14]. Additionally, recent research indicates that KT, or KT combined with therapeutic exercise, can have a substantial positive effect on patients with KOA [15]. Appropriate therapeutic exercise prescriptions generally benefit KOA patients, with neuromuscular control exercises (NCEs) being particularly effective. NCE has the potential to improve balance, muscle activation, functional alignment, and joint stability in individuals with KOA [16]. A study shows NCE improves cartilage and lowers knee loads in mild KOA patients [17]. Personalized, advanced NCE improves patient outcomes and physical abilities, such as movement independence and knee strength, even in older, severe KOA patients [18]. Previous research suggests NCE may be more effective than pharmacotherapy in alleviating long‐term symptoms like swelling and stiffness, addressing mechanical issues, and reducing side effects from analgesics and anti‐inflammatory drugs [16]. A prior study examined the impact of an NCE program utilizing non‐elastic taping on the knee joint in patients with KOA [18]. However, no research has yet measured the effectiveness of combining KT and NCE. Nonetheless, this combination may represent an effective treatment strategy for managing KOA. Based on this, we have planned this study.

Therefore, the primary objective of this randomized controlled trial (RCT) is to evaluate the impact of 8 weeks of KT combined with NCE on pain reduction and functional improvement in patients suffering from KOA. Additionally, we intend to examine the impact of KT and NCE on other outcome measures, such as muscle strength, ROM, and functional mobility. We also aimed to assess the potential long‐term advantages of integrating KT with NCE beyond the immediate post‐intervention period, through a 6‐month follow‐up, and to assess the safety of this intervention. We hypothesize that participants receiving KT in addition to NCE will demonstrate significantly greater improvements in pain, physical function, and neuromuscular performance than those receiving sham KT with NCE.

### Research Question

1.1

Among adults aged 45–70 years with radiographically confirmed KOA, does KT combined with an NCE program, compared with sham KT combined with the same exercise program, lead to greater improvements in pain, physical function, and relevant outcomes immediately after the 8‐week intervention and at 6‐month follow‐up?

## Methods

2

### Study Design

2.1

This study is a multicenter, assessor‐blinded, RCT comparing the effects of KT with NCE (experimental group) versus sham KT with NCE (control group) in a 1:1 ratio among 80 KOA patients in Bangladesh. Each group's intervention lasts 8 weeks, with three sessions per week, followed by a 6‐month follow‐up. Primary and secondary outcomes were planned to be measured at baseline, post‐intervention, and follow‐up. The study obtained ethical approval and was registered in the Clinical Trial Registry. To ensure transparency, the study adhered to the 2013 SPIRIT (Standard Protocol Items: Recommendations for Interventional Trials) guidelines (Table 1). Additionally, the CONSORT (Consolidated Standards of Reporting Trials) statement guidelines will be utilized to ensure transparent reporting of the findings (Figure 1).

**Table 1 hsr273125-tbl-0001:** SPIRIT guidelines.

Timepoint	Enrollment	Allocation		Post‐allocation	
	−T_1_	T_0_	T_1_	T_2_	T_3_
Enrollment					
Eligibility screening	X				
Informed consent		X			
Demographic and clinical assessment			X		
Group allocation		X			
Intervention					
Experimental group			X	X	
Control group			X	X	
Assessment					
VAS			X	X	X
PPT			X	X	X
WOMAC			X	X	X
Muscle strength			X	X	X
ROM			X	X	X
TUG			X	X	X

*Note:* −T_1_ = pre‐study enrollment; T_0_ = group allocation; T_1_ = baseline before intervention; T_2_ = measurement after 8 weeks; T_3_ = measurement after 6 months.

Abbreviations: PPT, pressure pain threshold; ROM, range of motion; TUG, Timed UP and Go test; VAS, visual analog scale; WOMAC, Western Ontario and McMaster University Osteoarthritis Index.

**Figure 1 hsr273125-fig-0001:**
[figure not shown]
CONSORT flow diagram.

### Participants and Recruitment

2.2

Participants meeting the eligibility criteria were recruited from the four participating branches of the Centre for the Rehabilitation of the Paralysed (CRP), Bangladesh, through routine physiotherapy services, clinical records, and referrals. A trained research assistant who was not involved in intervention delivery or outcome assessment conducted the initial screening using a standardized eligibility checklist. Recruitment commenced in September 2025 and is expected to continue through December 2026, including follow‐up. Eligible individuals received detailed information about the study procedures, potential benefits and risks, confidentiality, and their right to withdraw at any time without affecting their usual care. Written informed consent was obtained before enrollment and any study‐specific assessment. Recruitment procedures were designed to ensure equitable and impartial participant selection across the participating sites.

